# Stepped-wedge cluster randomised trial of a smoking cessation counselling training programme for midwives treating women with functional health illiteracy and low socioeconomic status (PROMISE): a study protocol

**DOI:** 10.1186/s13063-020-04555-0

**Published:** 2020-07-07

**Keywords:** Smoking, Pregnancy, Midwifery, Protocol, PROMISE, Randomised controlled trial

## Abstract

**Background:**

In the Netherlands, midwives are required to use the ‘V-MIS’ (Minimal Intervention Strategy for Midwives) smoking cessation counselling protocol to help pregnant women quit smoking. This counselling protocol is often poorly implemented in midwifery practices. It may also be less suitable for pregnant woman with low socioeconomic status or functional health illiteracy. We created an adapted version of the V-MIS protocol that is intended to facilitate implementation in midwifery practices: PROMISE (PROtocol for growing up smokefree using a Minimal smoking cessation Intervention Strategy in the Early stages of life). For this adapted protocol, midwives use carbon monoxide meters, storyboard leaflets, and specific communication techniques for women with functional health illiteracy. They will receive a face-to-face training in using these materials and communication techniques.

**Methods:**

The effectiveness and implementation of PROMISE will be tested in a stepped-wedge cluster randomised controlled trial. We will randomise clusters of midwifery practices and departments in hospitals. We will then train them, subsequently, at regular intervals (‘steps’). At each step, practices that will receive training cross over from the control condition to the experimental condition. We will measure how well the PROMISE protocol has been implemented by assessing the rate of pregnant women that received detailed smoking cessation counselling from their midwives (primary outcome). Our secondary target group is pregnant women with functional health illiteracy and low socioeconomic status. Among them, we will assess smoking status and health-related outcome before and after pregnancy.

**Discussion:**

The PROMISE smoking cessation counselling protocol is intended to help midwives, OB-GYNs, and other obstetrics professionals to support pregnant women with smoking cessation.

**Trial registration:**

Dutch Trial Registry: NTR 6305/NL6158. Registered on 20 December 2016.

## Background

Smoking tobacco during and after pregnancy is a major preventable cause of perinatal deaths and serious health problems, such as miscarriage, foetal growth problems, low birth weight, and congenital heart defects [1–4]. In addition, children of smoking parents are at higher risk of developing nicotine dependence later in life and are more likely to be exposed to second-hand and third-hand smoke [5, 6]. This puts them at higher risk for health problems during infancy and makes them more likely to contract bronchial infections, meningitis, and asthma [7–11]. In the Netherlands, about 75 children start smoking every day [12].

While many (future) parents quit smoking before pregnancy or in the early stage of pregnancy, smoking among (future) parents is still prevalent in many countries [11]. In the Netherlands, 7.4% of pregnant women smoke during pregnancy [13]. Smoking during pregnancy is particularly common among women with a low socioeconomic status (SES) [14–18]. In the Netherlands, 16% of low SES pregnant women smoke during pregnancy, while 12% of middle-educated and 3% of highly educated women do [13]. Moreover, relapse after delivery is high: about 50 to 70% of women who quit smoking before or during pregnancy relapse within 6 to 12 months after giving birth, and about one third of women who quit in an early stage of their pregnancy will relapse during the second or third trimester [11, 18–20].

Primary obstetric care professionals play an important role in smoking cessation care for pregnant women in the Netherlands. The vast majority of pregnant women regularly visit either a midwife (primary care) or an OB-GYN (secondary care), and most receive post-natal care and ‘youth health care’ after giving birth [21]. Youth health care is a set of free municipal care services for children aged 0–18 [22].

Midwives have a 4-year professional degree, which includes over 18 months of clinical work [23]. They are trained in educating prospective parents about pregnancies and accompanied women in their pregnancy, birth, and post-natal period. They work autonomously in uncomplicated pregnancies. Only when health problems arise or are likely to arise will they refer clients to OB-GYNs in hospitals. OB-GYNs are medical doctors specialised in both gynaecology and obstetrics. Both midwives and OB-GYNs are completely covered under the national medical insurance system. Because almost all pregnant women visit either a midwife or an OB-GYN, the Dutch evidence-based guideline for treating pregnant women with tobacco addiction stresses the importance of obstetric care professionals in providing smoking cessation advice to pregnant smoking women and in preventing relapse after delivery [24].

Dutch midwives are required to use the ‘V-MIS’ smoking cessation protocol (Minimal Intervention Strategy for Midwives) [25–27]. Using this protocol is optional for OB-GYNs. The V-MIS is an effective, minimal intervention protocol for guiding pregnant women and their partners in smoking cessation. Based on a randomised controlled trial (RCT) in 1996, 12% of smoking pregnant women counselled with V-MIS remained continuously abstinent during pregnancy, versus 3% in the usual care group [28]. Despite its efficacy, the V-MIS protocol has not been well implemented in daily practice [29, 30]. Midwives tend to go through only a few of the seven steps of the protocol. This is likely due to a lack of time and communication skills [29].

OB-GYNs, post-natal care, and youth health care are also required to implement protocols for smoking cessation support, but they may opt for protocols other than the V-MIS protocol [25]. In the Netherlands, post-natal care nurses are trained at a vocational level and support mothers at home during the first 8 days after delivery (3–10 h per day). They educate mothers about breastfeeding, do regular health checks on both mother and child, and do various domestic chores for them. This post-natal care is completely covered under national medical insurance, and most Dutch women receive post-natal care after childbirth [21]. Dutch youth health care is a municipal health care system in the Netherlands that provides free national and preventive care services to young people aged 0–18. Parents of young children (0–12 years) visit the youth health care clinic regularly, where nurses and paediatricians check their children’s social, physical, and cognitive development [22]. Youth health care nurses educate parents about parenting and vaccinate young children against common diseases.

Both primary and secondary obstetric care in the Netherlands are coordinated through regional obstetric partnerships (in Dutch: ‘verloskundig samenwerkingsverbanden’). These partnerships usually consist of a single large hospital and the midwifery practices in its surrounding region. In many cases, post-natal care and youth health care are included in the partnership as well. Local obstetric partnerships provide a relevant platform for disseminating new smoking cessation protocols among obstetric professionals.

The Dutch Health Care Inspectorate recently concluded that multidisciplinary smoking cessation care has been poorly implemented in both primary and secondary obstetric care, post-natal care nurses, and youth health care [22, 27, 29]. This has been illustrated by the fact that in 2016, 27% of youth health care professionals did not discuss smoking cessation with smoking parents [22, 31]. Besides being poorly implemented, the current smoking cessation protocols also appear less suitable for people with low SES or functional health illiteracy. While smoking during pregnancy is most prevalent among low SES women [18, 32], it is important that smoking cessation counselling is sensitive to this target client group. This is even more the case for those with functional health illiteracy. It is estimated that about 12% of Dutch adults have poor functional health literacy skills and experience difficulties in interpreting health-related information and in communicating with health professionals [33]. It is therefore imperative that smoking cessation protocols are adapted for women with low SES or poor functional health literacy skills.

The ‘PROtocol for growing up smokefree using a Minimal smoking cessation Intervention Strategy in the Early stages of life’ (PROMISE) aims to address some of the limitations of the V-MIS smoking cessation protocol and focusses on effective communication towards pregnant women with low SES or poor functional health literacy skills. In order to assess whether PROMISE manages to address these limitations and prompts midwives and OB-GYNs towards effectively discussing smoking cessation with smoking pregnant women, we will perform a stepped-wedge RCT. This paper describes the development, content, and procedures of the PROMISE protocol and the design of the stepped-wedge RCT.

## Methods/design

### Study summary

For this study, we will train midwives and OB-GYNs to use the PROMISE protocol for helping pregnant women to quit smoking. These care professionals will use carbon monoxide meters, storyboard leaflets, and specific communication skills for women with functional health illiteracy. Our main objective is to improve the rate at which they discuss smoking cessation strategies with pregnant women. Using a stepped-wedge randomised controlled design, we will evaluate the effectiveness of the PROMISE protocol while it is being implemented in 23 midwifery practices and 3 obstetrics hospital departments across three regions in the Netherlands. Over the course of the study period, we will assess the rate at which midwives and OB-GYN discuss smoking cessations strategies with their clients (primary outcome). We will also collect data about the level of appreciation of PROMISE by all professionals (i.e. midwives, OB-GYNs, post-natal care nurses, and youth health care; secondary outcome). Finally, we will assess smoking status and other perinatal parameters among pregnant clients before and after delivery.

### Aims and hypothesis

The main goal of this study is to examine the effectiveness of the PROMISE protocol in obstetric care. We test whether PROMISE will improve the level of smoking cessation support by obstetric care professionals and whether these professionals become more effective in delivering this support. Our primary outcome measure is the rate at which primary obstetric care professionals (midwives and OB-GYNs) discuss specific smoking cessation strategies with pregnant women.

*Hypothesis*: We hypothesise that the rate at which midwives and OB-GYNs discuss specific smoking cessation strategies will increase after professionals have been trained to use the PROMISE protocol.

### Study design

We will use a stepped-wedge randomised controlled design to implement the PROMISE protocol in 23 midwifery practices and 3 obstetrics hospital departments across three regions in the Netherlands: Amsterdam-Noord, Zaanstreek-Waterland, and Heerenveen. In a stepped-wedge cluster RCT, a programme is gradually implemented among clusters of respondents (see Fig. 1) [34]. In this study, clusters of professionals in midwifery practices or hospitals will continue to use the current V-MIS protocol at first (usual care, control condition) and will switch to using the PROMISE protocol after receiving an extensive face-to-face training (experimental condition).

**Fig. 1 Fig1:**
[figure not shown]
Overview of clusters of midwifery practices. Midwifery practices from three regions will be randomly allocated to one of four steps. At each step, practices that received training cross over from the control condition (V-MIS/usual care) to the experimental condition (PROMISE)

We will train clusters of midwives and OB-GYNs, subsequently, at four regular intervals (‘steps’). At each step, practices that received training cross over from the control condition to the experimental condition. We will measure outcomes at baseline, at each of the four steps (2 months apart, step 1 starting 2 months after baseline) and 2 months after the last step.

This study has been registered in the Dutch Trial Registry (NTR 6305) and was exempt from medical ethics review by the Ethics Committee of the Erasmus Medical Centre in Rotterdam (MEC-2016-605).

### Study procedure

#### Regions

We have selected three regions for implementing the PROMISE protocol. Eligible regions (1) had at least 250 smoking pregnant women with low SES in the previous year; (2) were willing and capable to implement PROMISE within its obstetric partnership; (3) had a well-organised level of cooperation between midwives, OB-GYNs, post-natal care nurses, and youth health care; and (4) were not participating in any other tobacco-related research projects.

#### Midwives and OB-GYNs

After receiving informed consent from midwives and OB-GYNs, we will randomly assign their practices to one of four steps. We will follow a training and cross-over procedure in accordance to our stepped-wedge study design. At baseline, all clusters of practices will use the existing V-MIS protocol for supporting women to quit smoking (i.e. control group). Two months after baseline, we will train the first cluster of practices (i.e. step 1) and will provide them with the PROMISE materials. From that moment onwards, this first cluster will cross over to the experimental condition and will continue to use the new PROMISE protocol. We will train clusters 2, 3, and 4 subsequently, each at a 2-month interval. After training, these clusters also cross over to the experimental condition. This way, we will train all practices in 4 steps over a 10-month period and all practices will be using the PROMISE protocol from month 8 onwards. By gradually implementing the PROMISE protocol among clusters of practices, we will replicate a real-life implementation of protocols that require face-to-face training. The order at which practices will receive the face-to-face training will be randomised at the practice level and stratified by region. We had no inclusion or exclusion criteria for the midwives and OB-GYNs, other than being employed at one of the practices enrolled in our study. At the start of the study (January 2017), participating midwives will complete a baseline questionnaire (T0) about their level of support to smoking pregnant women. They will receive a similar questionnaire at each step of the study (T1–T4) and will receive a final questionnaire 2 months after the final step (T5). These questionnaires include our main outcome variables. Figure 1 provides a schematic overview of the training steps. Care professionals will receive no incentive for filling out the questionnaires, but those who complete the training will receive continuing education credits.

#### Post-natal care nurses and youth health care

Post-natal care nurses and youth health care professionals will be offered a face-to face training too. Contrary to the midwife training, their training will only focus on preventing relapse after pregnancy. As the performance of post-natal care nurses and youth health care professionals will not affect the main outcome of this study, the order at which post-natal care nurses and youth health care professionals receive training will not be randomised stratified by region. Instead, their training will be provided at a first come, first served basis. Post-natal care nurses and youth health care professionals will receive a baseline questionnaire before the training and one follow-up questionnaire 12 months after training. These questionnaires will be used for evaluating the materials and improving future materials for these professionals. Participants will receive no incentive for filling out the questionnaire, but those who complete the training will receive continuing education credits.

#### Pregnant women

Pregnant women will be recruited through the midwifery practices and hospitals. Eligible women (1) are 18 years or older, (2) have been 0–3 months pregnant, (3) are current smokers or have quit smoking within the 6 months before pregnancy, and (4) have been registered in a practice or hospital that takes part in PROMISE. We will have no exclusion criteria. Midwives and OB-GYNs will provide recruitment materials to potential participants and inform them about the study. After providing written informed consent through their midwife of OB-GYNs, participants will receive a baseline questionnaire after 8 weeks of pregnancy and follow-up questionnaires at 2 weeks after delivery (T1) and at 6 months after delivery (T2). In those questionnaires, we assess smoking status and ask about the support they received from their midwife or OB-GYNs, post-natal care nurse professional, and youth health care professional. Women will receive a gift voucher of 10 euros for each questionnaire they complete.

This study was conducted from January 2017 to December 2019. All professionals have participated from January 2017 onwards, and the first training session has begun in March 2017. Pregnant women were able to enrol until March 2018. Among care professionals, we collected data from January 2017 to December 2017 and among pregnant women from January 2017 to December 2019.

### Randomisation

We will use R 3.0 to randomise the order (step) at which midwifery practices and hospitals will be trained. Within each of the three regions, practices will be randomly allocated to one of the four training steps. Neither professionals nor pregnant women will be blinded to their allocation. The authors will also not be blinded to the allocated arm that participants are in.

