#### Statistical analyses

We will use a Generalised Linear Mixed Modelling analysis in SPSS 25+ or R 3.0+ to analyse sample-wide changes in our primary outcome over time. In stepped-wedge designed studies, data should be interpreted at population level [34]. This means that not individual changes, but sample-wide changes over time are used to test the effectiveness of the new protocol (similar to a repeated cross-sectional design). In our study, all care professionals fill out a questionnaire at each of the six time points. In this questionnaire, they indicate the number of smoking women they have seen in the past month and the number whom they provided detailed smoking cessation counselling.

We calculate the percentage of smoking women who received detailed counselling for each care professional at each of the six time points. As each care professional will attend one of four training sessions, all professionals switch from the usual care condition (control) to the experimental condition at one of those time points.

Using a Generalised Linear Mixed Modelling (GLMM) analysis, we will analyse whether professionals provided detailed counselling to a higher portion of their smoking clients after receiving the training than before. We will include the factors ‘cluster’ (i.e. practices) and ‘individual’ (i.e. midwife/OB-GYN) as random effects, and ‘step’ will be included as fixed (time) effect. The exact link function (e.g. nominal, binominal) for the model will be based on the outcome variable. We will conduct an intention-to-treat analysis to control for lost to follow-up. Only members of the research team will have access to the research data.

As we do not anticipate any adverse effects in any of the two intervention arms, we will not conduct any interim analyses to determine if the trial needs to be stopped.

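### Training order is stratified by region, but the primary model has no region term, so the reported standard error of the training effect is slightly too wide

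*Protocol article*

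**What the plan says.** Two places in the protocol article describe the randomisation, and they agree. Under Midwives and OB-GYNs: "The order at which practices will receive the face-to-face training will be randomised at the practice level and stratified by region". Under Randomisation: "Within each of the three regions, practices will be randomly allocated to one of the four training steps". Region is the only stratification factor described.

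The Statistical analyses section names the terms of the primary generalised linear mixed model: "We will include the factors ‘cluster’ (i.e. practices) and ‘individual’ (i.e. midwife/OB-GYN) as random effects, and ‘step’ will be included as fixed (time) effect". It leaves the link function to be chosen later. It mentions neither region nor any other adjustment for the stratified allocation.

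The Study design section gives the size of the trial: the team will "implement the PROMISE protocol in 23 midwifery practices and 3 obstetrics hospital departments across three regions in the Netherlands". That makes 26 randomised units. Each unit is measured six times: at baseline, at each of four steps, and two months after the last step. Every unit moves from usual care to PROMISE.

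**The concern.** When allocation is stratified, the design removes between-stratum differences from the comparison. The analysis gets credit for this only if the stratification factor is in the model. Without it, the model counts variation between regions as variation between practices and treats it as a source of error, although steps have been balanced across regions. The estimate stays unbiased, but the reported standard error is too large and some power is given away.

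Regions could differ. They are three separate obstetric partnerships, and counselling habits may be shared within a partnership. What matters is how large the loss can be in a design where each practice acts as its own control.

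**Working it through.** **Figures in the plan.** The article gives no between-region variance, so no stated figure can be reproduced on this exact point. The Sample size section gives rates of 35% and 60%, two-sided alpha 0.05, power 0.80 and a between-cluster CV of 0.3. As a check on how the CV is used, I took the Hussey-Hughes variance with four clusters, five time points, between-cluster SD 0.3 x 0.35 = 0.105, and residual variance (0.35 x 0.65 + 0.60 x 0.40)/2 = 0.234. This returns the article's 18 professionals per cluster (power 0.81). An SD of 0.105 is therefore a reasonable reading of the plan's own input.

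**Inputs.**
- From the article: 26 practices or departments, 3 regions, 4 steps, 6 time points, effect 0.60 - 0.35 = 0.25.
- Assumed: 2 professionals per practice (54/26 is about 2); practices split 9/9/8 over regions (14/8/4 gives almost the same results); practice SD 0.105 (0.3 x 0.35) or 0.1425 (0.3 x 0.475, the mean rate); individual SD 0.10; residual variance 0.05 or 0.2375; between-region SD 0, 0.05, 0.105 or 0.20; a linear scale; and a training-condition term in the model.

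**Method.** Generalised least squares, with X holding training condition and six time effects, with or without two region indicators.
- Reported variance = condition element of B = (X'W⁻¹X)⁻¹, where W is the covariance that the fitted model believes.
- True variance = condition element of B X'W⁻¹ V W⁻¹X B, where V includes the regional component.
- Without region terms, the practice variance in W becomes practice SD² + region SD². For example, 0.105² + 0.105² = 0.022.

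**Results (9/9/8 split; SE without region / SE with region).**

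| Region SD | Practice SD | Residual | True SE | Ratio | Reported SE | Ratio |
|---|---|---|---|---|---|---|
| 0.105 | 0.105 | 0.05 | 0.0461 / 0.0458 | 1.006 | 0.0466 / 0.0458 | 1.017 |
| 0.105 | 0.105 | 0.2375 | 0.0933 / 0.0928 | 1.006 | 0.0952 / 0.0928 | 1.026 |
| 0.105 | 0.1425 | 0.05 | 0.0466 / 0.0465 | 1.003 | 0.0469 / 0.0465 | 1.009 |
| 0.105 | 0.1425 | 0.2375 | 0.0953 / 0.0949 | 1.003 | 0.0966 / 0.0949 | 1.018 |
| 0.20 | 0.105 | 0.05 | 0.0468 / 0.0458 | 1.021 | 0.0473 / 0.0458 | 1.032 |
| 0.20 | 0.105 | 0.2375 | 0.0957 / 0.0928 | 1.031 | 0.0986 / 0.0928 | 1.062 |
| 0.20 | 0.1425 | 0.05 | 0.0470 / 0.0465 | 1.011 | 0.0474 / 0.0465 | 1.019 |
| 0.20 | 0.1425 | 0.2375 | 0.0968 / 0.0949 | 1.020 | 0.0992 / 0.0949 | 1.045 |

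At region SD 0.05 the reported SE is 0.2-0.7% too wide and the true SE changes by no more than 0.1%. With no regional variance at all, including region costs less than 0.1% of the SE.

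The 0.20 rows are extreme. With practice SD 0.105, region would carry 0.04/(0.011 + 0.04), or 78%, of the between-practice variance.

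**Power from the reported SE**, as Φ(0.25/SE - 1.96), with practice SD 0.105 and residual 0.2375:
- Region SD 0.105: 0.25/0.0952 - 1.96 = 0.67, about 75%, without region; 0.25/0.0928 - 1.96 = 0.73, about 77%, with region.
- Region SD 0.20: 0.25/0.0986 - 1.96 = 0.58, about 72%, without region; about 77% with region.

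**The case against.** **The cost is almost nil.** Each practice lies in one region, so a constant regional difference is already absorbed by the practice random effect. The training effect rests mainly on before-after contrasts within practices. This stands: the true SE changes by well under 1% unless regional differences are extreme. A reader might infer that leaving region out biases the result or seriously weakens the trial. The documents do not support that. The omission only makes inference slightly conservative.

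**An article is condensed, and its list of terms may not be complete.** The list does not name a training-condition term either, although the same paragraph plainly intends a comparison of after with before training. The full protocol or analysis plan may contain region. This stands in part. Still, the section specifies the random and fixed effects and leaves only the link function open, so the model as written does not follow the randomisation.

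**Should setting be added too?** A reader might infer this from the Background statement on V-MIS, "Using this protocol is optional for OB-GYNs", and from the fact that three hospital departments cannot cover four steps. The documents do not carry that far. Setting is not a stratification factor. The Background sentence describes Dutch practice in general, whereas the section on the control condition says that all participating practices and hospitals use V-MIS and were trained in it. Any effect also depends on an assumed difference between settings. At 15 points, chance placement of the departments shifts the estimate by 0.3-0.9 points on average and 2.4 at worst. With 15-25 points and slightly different inputs, the worst allocation gives 1-5 points. The SE is 5-10 points. I do not press this.

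**Region main effects do not deal with regional differences in time trend.** This is true. Such differences would need region-by-step terms, and in the runs made these changed the SE by no more than about 1%.

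**Conclusion.** The point holds in a limited form. The training order is stratified by region and the stated primary model does not reflect this. As a result the reported SE of the training effect is too wide by about 1-2.6% at a between-region SD of 0.105 and 2-6% at 0.20. The corresponding true loss of precision is about 0.3-0.6% and 1-3%. There is no bias.

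The omission itself is clear from the text. Its size rests on assumed variances, on about two professionals per practice, on a linear approximation to the mixed model, and on regional differences that are constant over time. It is worth correcting because the correction is nearly free, not because the conclusions are at risk.

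**What to change.** In the Statistical analyses section, add region (three levels) as a fixed effect in the primary mixed model, beside the fixed effect for step, and state that it is there because allocation was stratified by region. Practice and individual stay as random effects.

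The cost is one line of wording and 2 degrees of freedom. Region is known for every record, so no new data are needed. By the article's own dates, data collection among professionals ended in December 2017, before publication in July 2020. The addition should therefore be dated and justified by the randomisation. If the model has already been fitted without region, report both fits.
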